### Strategies to improve adherence to interventions {11c}

Women will be reminded to complete questionnaires via the app’s calendar function and by email and phone.

### Relevant concomitant care permitted or prohibited during the trial {11d}

Participation in the study does not require any change in usual care pathways (including taking medications or providing standard health promotion and prevention information), and these will be maintained for both study arms.

### Provisions for post-trial care {30}

There is no anticipated harm and compensation for study participation.

### Outcomes {12}

The primary study outcome is the differences between experimental and control groups regarding adherence to DPT vaccination in pregnant women (questionnaires; evaluation at T3—postpartum period). The choice of this outcome is due to the clear evidence of the need for maternal vaccination, especially against pertussis, which can be a life-threatening infection for the newborn. Moreover, available data on DPT vaccination coverage among pregnant women in Trieste for the past years show an unsatisfactory percentage of women vaccinated with DPT (only 55%).

Secondary study outcomes are the differences between experimental and control groups in:Knowledge and behaviours in terms of health prevention and promotion, especially regarding folic acid intake, weight gain during pregnancy, smoking and alcohol consumption, breastfeeding, adherence to the routine childhood immunization schedule (questionnaires; evaluation at T1—end of the second trimester, T2—end of the third trimester, T3)Level of health literacy (Italian version of the 16-item European Health Literacy Survey Questionnaire HLS-EU-Q16; evaluation at T1, T2, and T3)Evaluation of the social and health impact of the introduction of an mHealth app for a maternal and child hospital (questionnaire; evaluation at T3)

As with the experimental group, the final evaluation will include:The appreciation of such a tool to bridge the information gap between patients and health institutions (qualitative satisfaction questionnaire, freely modified from the Mobile Application Rating Scale (MARS); evaluation at T3)Analysis of data on app use collected by the app itself throughout the study period

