Data on app use (frequency of app access, content consultation, references consultation, use of app features, etc.), access to and use of health services, and vaccination adherence during pregnancy will also be collected with support from the regional health information systems.

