### Participant timeline {13}

Pregnant women will participate in the study from the first antenatal echography until the end of the first 1000 days of their child’s life. The evaluation time points are enrolment in the study (T0), end of the second trimester (T1), end of the third trimester (T2), and the postpartum period (T3). Data on app use will be collected throughout the study period. Other variables collected (T0) include data describing the population and potential confounders (e.g. age, country of origin, marital status and composition, socioeconomic level, educational level) and risk/protective factors (e.g. smoking and alcohol habits before pregnancy, data on current pregnancy).

Data collection will be based on self-completed questionnaires in paper form (T0, T1, T2) and online (T3), as well as data collected using information and management systems, and data on app use.

The questionnaires are provided as a Supplementary Material to this study protocol. Additional data to confirm vaccination adherence and to monitor access to and outcomes of preventive health, health promotion, and care can be accessed through the regional health information systems.

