## Assignment of interventions: blinding

### Who will be blinded {17a}

None, this is an open-label study.

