## Statistical methods

### Statistical methods for primary and secondary outcomes {20a}

Categorical variables will be presented as absolute numbers and percentages; continuous variables will be presented as mean and standard deviation or median and interquartile range, depending on data distribution assessed visually and using the Kolmogorov–Smirnov test.

The main population characteristics of the participating women in both groups (age, marital status, living area, country of origin, socioeconomic level, educational and occupational level, etc.) will be compared to assess the effectiveness of randomization. Differences between the two groups on categorical outcomes will be assessed using the chi-square test or Fisher’s exact test, as appropriate. Comparisons between continuous variables will be made with nonparametric Student *T* or Mann–Whitney tests, as appropriate for the data distribution. The main analysis will be an ‘intention-to-treat design’: all randomized women with an available main outcome will be assigned to the associated group regardless of intervention. A per-protocol analysis will also be performed. A statistically significant difference will be considered to exist if the *p*-value is < 0.05.

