## Discussion

Despite the unpredictability of the COVID-19 pandemic in the next few years, support from this mHealth tool will be a constant; furthermore, access to maternal and child health care will not be reduced because these services are considered essentials. Loss during the follow-up period is likely the greatest risk for this study. Several reminder measures have already been planned to address this risk, including email, phone calls, and reminders via the app’s calendar.

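### The primary outcome rests on unblinded self-report at T3, although regional vaccination records are already to be collected and no rule says which source prevails

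*Protocol article*

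**What the plan says.** The Outcomes section {12} of the protocol article sets both source and time of the primary outcome: "adherence to DPT vaccination in pregnant women (questionnaires; evaluation at T3". The Participant timeline {13} describes the instrument: "Data collection will be based on self-completed questionnaires in paper form (T0, T1, T2) and online (T3"). On blinding, section {17a} answers "None, this is an open-label study".

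A second source for the same event is planned. The Intervention description {11a} says that "vaccination adherence during pregnancy will also be collected with support from the regional health information systems", and Data management {19} merges health-information-system data into the final data set. On these regional data the Participant timeline {13} is weaker: "Additional data to confirm vaccination adherence and to monitor access to and outcomes of preventive health, health promotion, and care can be accessed". Plans for assessment {18a} repeats this weaker form.

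The main analysis ({20a}, and likewise {20c}) takes "all randomized women with an available main outcome". Section {20c} adds a sensitivity analysis for missing data. The Discussion states: "Loss during the follow-up period is likely the greatest risk for this study".

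The app is given to group A. It covers immunisation in pregnancy, carries the T3 form alongside the institute's online platform ({11a}), and its calendar is one reminder channel beside email and phone ({11c}, {18b}).

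**The concern.** The text leaves three questions open for the one comparison the trial is powered for.

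1. If the T3 answer and the regional record disagree, which one is the primary outcome? Read literally, section {12} says the questionnaire.
2. If T3 is not returned but a regional record exists, is the main outcome available? No section says.
3. Is ascertainment alike in the two arms? Group A women know their allocation, have been shown material favouring vaccination, and have an extra route and an extra prompt to return the form. Over-reporting and non-response may therefore differ by arm.

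If they do, the estimated effect mixes vaccination with reporting and response. Dependence on T3 also exposes power to the loss that the protocol itself names as its main risk. Much of this exposure looks avoidable, because access to a source that does not depend on the woman's own report is already planned.

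**Working it through.** **Inputs from the documents** (Sample size {14}): 55% against 70%, alpha 0.05, power 80%, 163 per group, 180 per group to be recruited. The documents give no misreporting or T3 response rates, so those used below are assumptions.

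**The plan's own figure.** Two-sided, pooled variance, no continuity correction, mean proportion 0.625:

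n = [1.960 × √(2 × 0.625 × 0.375) + 0.842 × √(0.55 × 0.45 + 0.70 × 0.30)]² / 0.15² = (1.342 + 0.569)² / 0.0225 = 162.3, so 163. The stated size reproduces.

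**Power by outcome availability.** Power = Φ[(0.15√n − 1.342) / 0.676].

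| Outcome available | n per arm | Power |
|---|---|---|
| 100% | 180 | 83.9% |
| 90% | 162 | 79.9% |
| 80% | 144 | 75.1% |
| 70% | 126 | 69.3% |

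The planned allowance is 17/180 = 9.4%, and it must also cover spontaneous abortion.

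**Differential over-reporting, no true effect.** The true rate is 55% in both arms. A share f of unvaccinated group A women report vaccination and none in B do. False difference = 0.45 × f. Two-sided rejection at 163 per group:

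| f | Reported A vs B | False difference | Type I error |
|---|---|---|---|
| 5% | 57.25% vs 55% | 2.3 points | 6.9% |
| 10% | 59.5% vs 55% | 4.5 points | 13.0% |

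**Differential response, no true effect.** In group A, 90% of vaccinated women return T3 and a share r of the unvaccinated do. In group B, response is unrelated to vaccination. Observed rate in A = 0.55 × 0.90 / (0.55 × 0.90 + 0.45 × r):

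- r = 85%: 56.4%, a false 1.4 points
- r = 80%: 57.9%, a false 2.9 points
- r = 70%: 61.1%, a false 6.1 points

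**Equal misreporting in both arms.** This works the other way. With sensitivity and specificity both 95%, the 15-point effect shrinks to 68.0% − 54.5% = 13.5 points, and power at 163 per group falls to 70.8%. With both at 90%, it shrinks to 66.0% − 54.0% = 12.0 points, with power 60.0%.

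**The case against.** The strongest reply is that an objective source is not absent. The regional data are to be collected ({11a}) and merged ({19}), so the gap is a rule of precedence between two planned sources. That stands, and it is how the point should be read. It does not remove the gap: confirmation without a rule for disagreement leaves the questionnaire as the outcome.

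A reader might infer that women who do not return T3 are dropped from the main analysis. The documents do not say so. The condition in {20a} and {20c} is an available outcome, not a returned form, and after the merge a regional record might satisfy it. What can be said is that this is unsettled.

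A reader might also infer that bias by arm is established. It is not. Standard care also includes education on immunisation in pregnancy ({6b}) and continues in both arms ({11d}), so some over-reporting in B is plausible and would shrink the false difference. Assuming none in B is the extreme case, and equal misreporting dilutes the effect. Email and phone reminders are also planned besides the app calendar.

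Nor do the documents support calling T3 late. It is dated only as postpartum.

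The sensitivity analysis in {20c} helps with non-response. It does not address misreporting.

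Finally, regional records may be incomplete. Their coverage is not documented, and the fix has to allow for that.

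**Conclusion.** The concern holds in this form: the protocol fixes the primary outcome on unblinded self-report at T3, plans a more objective source for the same event, and does not say which prevails or whether the regional record counts when T3 is missing. Reporting and response may differ by arm. The documents do not show that they do, nor in which direction.

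The sizes are illustrations. With 5% to 10% over-reporting in unvaccinated group A women and none in B, the false difference is 2.3 to 4.5 points against a 15-point target, and type I error is 6.9% to 13.0%. If 20% to 30% of T3 forms are lost and no other source is used, power is 75% to 69%, against 84% with the outcome known for all 180 per arm. That last figure is an upper limit, because a regional record does not recover women excluded after pregnancy loss.

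**What to change.** Define the primary outcome in {12} as DPT vaccination during pregnancy recorded in the regional health information system. Extract it without sight of arm, for all randomised women in the analysis population, whether or not T3 is returned. In addition:

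- Reconcile that population with section {11b}, which removes women after intrauterine death, severe foetal malformation, miscarriage or therapeutic abortion.
- In the main analysis, count women whom the regional system covers but who have no record as unvaccinated. Letting the T3 answer override a missing record would bring self-report back into the group most able to over-report.
- Use the T3 answer only for women whom the regional system does not cover, for example non-residents.
- As sensitivity analyses, report agreement between the two sources by arm and repeat the comparison on self-report.
- Align {11a}, {12}, {13}, {18a} and {20c}, so that collection of regional data is firm throughout and an available outcome is defined.

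The cost is a few sentences. Access to the regional data is already planned, the requirement of 163 per group does not change, and the Trial status section says recruitment has not begun. The downside is that some doses given outside the region may be missed; the sensitivity analyses would show how much that matters.

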
### Objectives {7}

People are increasingly using eHealth and mobile health solutions thanks to the ease of access and rapid communication digital solutions provide. While this brings a variety of benefits and new opportunities, it may also pose a threat to public health in terms of prevention and health promotion by exposing them to potential risks such as lack of control and fake news.

The authors seek to answer the following research questions:Is an mHealth app a potential tool to bridge information and communication gaps between patients and institutions in the first 1000 days of life?What are the health and social implications of a patient- and family-centred mHealth application in a maternal and child health institute?Could such a tool be useful for supporting pregnant women and new mothers in the first 1000 days of life?Could such an mHealth tool be used at a regional or national level to improve the relationship between citizens and healthcare providers?

The primary aim is to evaluate the effectiveness of the mHealth app in supporting women in the first 1000 days (from conception to 24 months of life) and improving health behaviours, e.g. immunizations during pregnancy, weight gain during pregnancy, abstaining from smoking and alcohol consumption, and adherence to the routine childhood immunization schedule.

The secondary aim is to explore the level of appreciation of this mHealth app as a tool to bridge information and communication gaps between patients and healthcare providers.

Our findings will be relevant to improving this mHealth app to promote health and prevention and support the first 1000 days of life for mothers and children. Our findings will be relevant to the future expansion of such an mHealth app to promote positive health-related outcomes for patients and co-user satisfaction and to support the organization of healthcare services.

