### Intervention description {11a}

Both groups of women (A and B) will be asked to complete an initial questionnaire to collect demographic and other data at time zero (T0). This paper questionnaire includes questions on health literacy, knowledge, and attitudes toward prevention and health promotion behaviours. At the same time, women in the experimental group will be assisted to download and instal the mHealth app on their smartphone or tablet.

During the study period, women in group A will be able to use the app, which was developed in collaboration with Area Science Park to support the first 1000 days of life, with all its features and content, while women in group B will be exposed to standard care. Specific content will be presented to the user according to the current pregnancy trimester or postpartum period following a scheduled routine; in any case, all content will always be available for free consultation throughout the usage period. Links to relevant institutional websites for further information will also be provided. The app will also include a FAQ (frequently asked question) section and a calendar function with the ability to set appointments and reminders. The app’s content and topics will include information on health preventive behaviours such as immunizations during pregnancy, weight gain during pregnancy, smoking abstinence and alcohol use, and adherence to routine childhood immunization schedules. The app will be an informative and educational tool aimed at improving health behaviours and well-being.

Three additional questionnaires will be collected from both groups of women during the study period at the end of the second and third trimesters (T1–2) and during the postpartum period (T3). While the second and third questionnaires will be distributed in printed form according to the women’s planned access to the Unit of Fetal Medicine and Prenatal Diagnosis, IRCCS "Burlo Garofolo", the fourth questionnaire will be made available online on the IRCCS "Burlo Garofolo" platform and in the app itself. Women will be reminded to complete it through the app’s calendar function and through email and phone reminders.

At the end of the trial period, women will also be asked to rate their appreciation of the app features and content by providing feedbacks in digital form and participating in focus group sessions.

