### Recruitment {15}

Women attending the Unit of Fetal Medicine and Prenatal Diagnosis, IRCCS "Burlo Garofolo", in Trieste for the first echography of their pregnancy (around 12° gestational week (gw)) will be screened according to the inclusion and exclusion criteria outlined previously. The women concerned will be offered participation in this study. Recruitment will be kept open until the required sample size is reached; recruitment is expected to last 3.5 months. Since all women living in the area of Trieste will be required to visit the IRCCS "Burlo Garofolo" public health institute in Trieste for the first pregnancy echography, this will allow the researchers to reach the required number of participants.

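### Folic acid, smoking and alcohol outcomes are not limited to behaviour after enrolment at about 12 weeks and are tested unadjusted, so behaviour already settled by T0 dilutes these secondary comparisons

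*Protocol article*

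**What the plan says.** **Start of exposure.** Under Recruitment {15}, women attending the unit "for the first echography of their pregnancy (around 12° gestational week (gw)) will be screened". Intervention description {11a} has both arms complete the T0 questionnaire and continues: "At the same time, women in the experimental group will be assisted to download and instal the mHealth app". No participant therefore has the app before about 12 weeks.

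**Outcomes.** Outcomes {12} lists as a secondary outcome knowledge and behaviours, "especially regarding folic acid intake, weight gain during pregnancy, smoking and alcohol consumption", together with breastfeeding and the childhood immunisation schedule. The timing is "evaluation at T1—end of the second trimester, T2—end of the third trimester, T3". No period is given for the intake or consumption to be reported.

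**Baseline data.** Participant timeline {13} gives, as examples of risk and protective factors collected at T0, "smoking and alcohol habits before pregnancy, data on current pregnancy". What the second item contains is not spelled out.

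**Analysis.** Statistical methods {20a} names chi-square or Fisher tests for categorical outcomes, with no adjustment for T0 status. Methods for additional analyses {20b} plans none.

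**Aim.** Objectives {7} speaks of "supporting women in the first 1000 days (from conception to 24 months of life".

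**The concern.** An intervention can change only what happens after it starts. A woman who stopped smoking or drinking before the scan and stays stopped is a non-user at T1 to T3 in either arm. Folic acid taken before the scan was taken without the app. If a T1 to T3 item asks about use during the pregnancy as a whole, part of the answer was fixed before randomisation. If it asks about current use, women whose behaviour was already settled still make up part of both arms and shrink the absolute difference between them.

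What is at stake is how these secondary results will be read. With the contrast confined to a minority of women and no use made of T0 status, a null result on smoking, alcohol or folic acid says little about whether the app works in those who could still change.

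**Working it through.** **1. The plan's own figure.** The only calculation in the protocol is for the primary outcome: DPT vaccination 55% versus 70%, alpha 0.05, power 0.80, from Sample size {14}. With the pooled normal approximation, two-sided:

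n = [1.96·√(2·0.625·0.375) + 0.8416·√(0.55·0.45 + 0.70·0.30)]² / 0.15² = (1.342 + 0.569)² / 0.0225 = 162.3, so 163 per group.

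This agrees with the stated 163. The point below does not touch it.

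**2. Dilution in general.** Suppose a share f of women have behaviour fixed before T0, and the app shifts the rest by 15 points. The difference over all women is 15·(1 − f) points. To show the effect on power, I borrow the 55% base rate and 163 per group from the DPT calculation. The documents give no rates for folic acid, smoking or alcohol, so this is an illustration only. The formula, used again in step 4, is

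power = Φ( [ |p1 − p2| − 1.96·√(2·p̄(1 − p̄)/n) ] / √((p1(1 − p1) + p2(1 − p2))/n) ).

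| f | Difference over all women | Power |
|---|---|---|
| 0% | 15 points | 0.80 |
| 25% | 11.25 points | 0.55 |
| 50% | 7.5 points | 0.28 |
| 75% | 3.75 points | 0.10 |

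Only at f = 100% is an effect impossible.

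**3. How many women can still change: smoking, assumed figures.** If 20% (range 15–30%) smoked before pregnancy and 50% (range 30–70%) of them stopped before the scan, the number per arm of 180 still smoking at T0 is

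- central: 180 × 0.20 × 0.50 = 18, that is 10%;
- low: 180 × 0.15 × 0.30 = 8;
- high: 180 × 0.30 × 0.70 = 38.

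**4. What T0 status buys.** Take 18 smokers per arm at T0 and assume no uptake or relapse among the other women. For assumed stopping of 20% (control) versus 50% (app):

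- All women, unadjusted: smoking is 0.10 × 0.80 = 8% versus 0.10 × 0.50 = 5%, n = 180. The power is Φ((0.030 − 1.96·0.02599)/0.02594) = Φ(−0.81) = 0.21.
- T0 smokers only: 20% versus 50% stop, n = 18. The power is Φ((0.30 − 1.96·0.159)/0.151) = Φ(−0.08) = 0.47.

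The same steps for the other combinations of 10% or 20% against 50% or 60% give the table below. The last column is simulated (4,000 runs each): T0 smokers per arm drawn as binomial with n = 180 and probability 0.10, then Fisher's exact test among them at 0.05.

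| Stop, control vs app | Smoking over all women | Unadjusted, n = 180 | T0 smokers, normal approx. | T0 smokers, Fisher |
|---|---|---|---|---|
| 20% vs 50% | 8% vs 5% | 0.21 | 0.47 | 0.38 |
| 10% vs 50% | 9% vs 5% | 0.32 | 0.77 | 0.70 |
| 20% vs 60% | 8% vs 4% | 0.36 | 0.70 | 0.63 |
| 10% vs 60% | 9% vs 4% | 0.49 | 0.92 | 0.87 |

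The gain arises because conditioning on T0 status removes the chance difference between arms in the number of women who entered as smokers. All these figures treat women as independent. Allocation is by enrolment day, so the absolute values are, if anything, optimistic. The comparison between columns is what matters.

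**The case against.** The case on the other side is strong in several places.

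- **The outcome is measured after randomisation.** T1, T2 and T3 all follow T0. Continued use, later stopping, relapse, folic acid taken after the scan, and knowledge can all respond to the app. This stands. A reader might infer that these outcomes could not have been changed at all. The documents do not support that.
- **The protocol nowhere counts early quitting or first-trimester folic acid intake as an outcome.** This also stands. The reporting period of each item is in the questionnaires, a supplement that is not shown, and they may already ask only about behaviour since the last visit. To claim that the folic acid effect is zero by construction, one would have to assume a period that the text does not give. Deleting folic acid intake as an outcome is therefore not justified.
- **Randomisation balances earlier behaviour in expectation.** It does, so the consequence is lost power and not a false effect. Balance in expectation does not restore the power.
- **T0 may already capture current use.** The list there is introduced as examples and includes data on the current pregnancy. That may cover the recording. It does not alter the stated analysis, which makes no use of T0 status.
- **The aim says from conception.** One could read this as an aim that the design cannot answer. In context the phrase explains the term first 1000 days, and Participant timeline {13} says plainly that participation starts at the first scan. It is not a separate error.
- **The rates are assumed.** They are, and they show only direction and rough size.

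**Conclusion.** The concern holds in a limited form. Exposure starts at about 12 weeks, the Outcomes section sets no post-enrolment period for folic acid, smoking and alcohol, and the stated tests ignore T0 status. The consequence is dilution of secondary comparisons, in proportion to the share of women whose behaviour was settled before T0. There is no bias, and the primary outcome and its sample size are untouched.

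Under the assumed smoking figures, power rises from about 0.21–0.49 unadjusted to about 0.38–0.87 among T0 smokers by Fisher's exact test. This rests on 10% smoking at T0, no uptake or relapse among the others, complete outcomes and independent women. The true gain depends on rates that the protocol does not give.

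**What to change.** - **Participant timeline {13}:** make sure that current smoking, alcohol and folic acid use are recorded at T0, in addition to habits before pregnancy. If the data on the current pregnancy already include them, say so.
- **Outcomes {12}:** define these outcomes as behaviour after T0. Keep folic acid intake after enrolment and folic acid knowledge as outcomes, and treat earlier intake as a baseline characteristic.
- **Statistical methods {20a}:** analyse use at T1 to T3 adjusted for, or stratified by, T0 status.
- **Reporting:** word conclusions on these behaviours as applying from the first-trimester scan onward.

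The cost is one or two T0 items at most, some rewording and a slightly more complex secondary analysis. Trial status describes the trial as not yet recruiting, so the T0 items can still be settled before the first woman is enrolled. Afterwards, any missing T0 status could only be recalled.
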